### Statistical justification for sample size

2.11

#### Main study sample

2.11.1

Based on a participation rate in 2020 of 49% for the five participating departments (11) assuming a margin of non-inferiority of 2 points to demonstrate that participation is non-inferior in the intervention arm, and considering a power of 80% and a bilateral alpha risk of 5%, the number of women to be included is equal to 9,808 in each arm, being a total of 19,616 women.

There are 2,847 GPs in the five departments (42). Considering that GPs operate from 1,570 different practices (42) the number of women targeted per practice will be 48. With an average cluster size of 48 women and an intraclass coefficient of 5%, the number of subjects to be included to account for this cluster randomization must be multiplied by 3.35, or 65,647 women (32,824 per group).

The number of GPs included will be approximately 2,847 in the five departments. The recruitment potential is approximately 25,000 women per month (personal communication from the CRCDC). The inclusion will therefore be done over 3 consecutive months.

#### Ancillary study sample

2.11.2

In her article, Pérez-Lacasta observed a difference in the decision-making conflict scale score between women who received information and those who did not of 18.53 vs. 13.77 (standard deviation at 20.25) (43). On these assumptions, 762 responses would be required to arrive at a significant difference.

The ancillary survey conducted by questionnaire to assess SMDM quality will be carried out on an independent sample of 5,000 women, equally divided between the 2 arms. Based on a response rate of 20%, the number of questionnaires collected will be 1,000.

### Justification of the non-inferiority margin

2.12

In a non-inferiority trial, the margin chosen must meet two criteria: (i) be less than the differences observed in the superiority trials already conducted, and (ii) be less than the Minimal Clinically Important Difference.

International evidence on whether the use of DAs changes participation in the OS is scarce, without clear direction. It may therefore result in an increase (44) or a decrease in participation rates (45). Recent studies do not show a change in participation rates when women are invited to participate in decision-making (43, 46, 47).

The non-inferiority margin was set at 2% in agreement with the BC OS medical experts at the CRCDC. This is the largest difference in clinically acceptable OS participation. The Cochrane literature review reports an average of 1 death averted per 2,000 women screened over 10 years (44), the observation of 10 healthy women who would not have been diagnosed if they had not participated in screening and who will be treated unnecessarily (44). Thus, of the 75,000 women who will be included in the study, and according to our participation hypotheses, a 2% decrease in participation in the intervention group would imply the non-screening of 750 women. No additional deaths from BC are expected following the procedure, but between 3 and 4 women will not be treated unnecessarily.

The trial will therefore be conclusive if the lower bound of the two-sided 95% confidence interval of the difference in participation between the randomization arms is greater than 2.

### Status and study schedule

2.13

The beginning of the intervention will correspond to letters being sent to the included women and their GPs (T0).

The ancillary study will begin 2 months after T0, with a follow-up at 2 months.

Patients will be followed for 18 months. The freezing of the OS participation database within 18 months will be carried out 30 months after the intervention (M30). This schedule takes into account the time required for data entry. All statistical analyses and valuations of results will be conducted from M30.

**Table 2** presents the time schedule for enrolment, intervention, and assessments.

**Table 2 T2:** Time schedule for enrolment, intervention and assessments.

	Study period									
	Enrollment		allocation	Postallocation						Closeout
**TimePoint**		_t_1_	0	t_1_	t_2_	t_3_	t_4_	t_5_	… T_18_	T_30_
**Enrollment:**										
Eligibility screen		X								
Inform consent (main study) Inform consent (ancillary study)			X		X		X			
Allocation			X							
**Interventions:**										
Decision aid for organized cancer screening				X	X	X			…. X	
Standard organized cancer screening				X	X	X			…. X	
**Evaluations:**										
Proportion of women aged 50 to 74 who had a screening mammogram 18 months after the procedure.										X
Participation rate 18 months after the intervention according to age, socio-economic level, medical follow-up, presence of a chronic pathology, psychiatric pathology, previous participation in screening.										X
SDM-Q9 and DCS scores 2 months after the start of the intervention.										X
Answers to the intention to participate questionnaire, answers to the knowledge questionnaire 2 months after the start of the intervention.										X

SDM-Q9, Shared Decision Making Questionnaire; DCS, Decisional Conflict Scale. X = realization of the stage.

### Patient involvement

2.14

Women were involved in designing and developing the DA.

### Data storage and retention

2.15

Directly identifying and pseudonymized data relating to women and professionals willing to participate in the research will be kept in active database, in the CRCDC and French health insurance system information systems, up to two years after the last publication of the research results or, in the absence of publication, until the final research report has been signed. Pseudonymized data will also be kept in additional archives by archiving on paper and computer media for a period of fifteen years. These durations are based on the regulations applicable to research compliant with MR003 Reference Methodology, according to deliberation 2018-154 of May 3, 2018.

This study protocol has been prepared according to the 2013 SPIRIT guideline for clinical trial protocols (48). It was recorded in ClinicalTrials.gov (number NCT05607849, November 7, 2022; Version 1).

## Discussion

3

### Results and expected benefits of the DEDICACES study

3.1

The DEDICACES (“*DEcision partagée dans le cadre du DépIstage du CAnCEr du Sein en soins premiers*”) study should make it possible to evaluate whether the provision of a French DA (in accordance with international standards, built with patients and professionals) modifies participation in BC OS. At the end of the study, the research team expects to demonstrate that providing a better explanation of the benefits and risks of BC screening is not at odds with screening participation. Some women may choose not to participate, while others may choose to participate. In total, the average participation could therefore remain equivalent to the current participation rates. In addition, providing a DA without modifying participation would be significant progress in informing women and reducing decision-making conflict (and therefore better adherence). In this scenario, DA and SMDM on cancer screening for women would also meet societal demands for greater ethical practice in medical care for individuals.

While formalized SMDM practices in France are still rare, the study should make GPs aware of SMDM in BC screening. It will thus increase GP expertise on this topic and enable them to better answer their patients’ questions potentially leading to an increase in the number of women participating in screening.

Finally, the main perspective of the study is the generalization of DAs, which will be made available to women and healthcare professionals involved in BC screening.

Foreign literature has fed into the reflection of this study. International evidence on whether DA use modifies screening participation is scarce and results are contradictory (24, 44, 45, 49). A Cochrane literature review (44) reported that better informing women about their cancer risk and screening may increase participation, reporting a low level of evidence based on 3 studies (44, 50). On the other hand, the DECIDEO study born conducted in France reported a (limited) decrease in participation, estimated at 2% (45). Controlled trials have been performed evaluating tools to measure the effectiveness of shared decision interventions. These improve women’s knowledge about participation options and promote clear choices for BC screening (43, 51–53). On the other hand, the results for decision regret and decision conflict are more variable (43, 49, 52, 54, 55). There is uncertainty about whether interventions targeting both patients and healthcare professionals increase SMDM, compared to an intervention targeting either member of the pair (27). Furthermore, while factors associated with low participation have been widely described (28, 29, 56–58) literature does not report a relationship between DA availability and improved use of screening mammography for women meeting the criteria associated with lower participation.

Overall, these studies reveal the need for a robust and large-scale evaluation as we propose in this protocol. The central role of the regular GP in the care pathway, makes France an ideal location to conduct this study.

### Strengths and limitations

3.2

The proposed research is characterized by the robustness of the design. Randomization is performed on GP medical practices with the aim of limiting confounding bias between arms. Research is also distinguished by its power; it is conducted in a region of western France, with differences in ease of access to healthcare professionals and screening participation. The trial will include several thousand women, about 4 to 30 times more than other studies evaluating DAs for screening mammography (24). Finally, the study is characterized by its reproducibility. The design is built with the intention of screening, and the intervention is easily reproducible.

There are some limitations. The content of the consultation with the GP cannot be studied. The ancillary study, which will be conducted on a small sample of women, will provide initial answers about SMDM quality using a questionnaire. Low response rates to postal questionnaires may limit the available data for this analysis. However, the use of prepaid return envelopes and a reminder should increase the response rate to questionnaires.

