### Statistical analysis

2.10

All data will be described globally and by randomization arm. The research is a non-inferiority clinical trial. The statistical unit is the woman eligible for screening. The materiality threshold will be set at 5% in a bilateral situation. Statistical analyses will be performed using R 3.6.0 software (R Foundation for Statistical Computing, Vienna, Austria. URL https://www.R-project.org/).

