#### Exploratory secondary analyses

2.10.2

Participation rates in exploratory subgroup analyses will be studied in the same manner as the primary endpoint. The same margin of non-inferiority will be used. There is no provision for alpha risk adjustment for these analyses. The different subgroups are: (i) women aged 50 to 59/60 to 69/70 to 74 years at baseline, (ii) beneficiaries/not beneficiaries of the Complementary Solidarity Health at baseline, (iii) women who consulted/did not consult at least one GP, gynecologist or midwife (during the follow-up period for women who did not have a bilateral mammogram during the 18 months, or from baseline until the date of the bilateral mammogram for women who had the screening) (iv) women residing in a municipality with a low deprivation index (per quintile of the deprivation index) (41).

Predictors of OS use will be assessed using a multivariate generalized mixed model fitted to the physician as a random effect, and as fixed effects: (i) the number of visits to the treating physician, GP, gynecologist, or midwife in the 18 months prior to enrolment, and from baseline to bilateral mammography or to the end of the follow-up period for women who did not have bilateral mammography, (ii) the woman’s age at baseline, (iii) the presence of a chronic condition measured *via* chronic drug use and testing, (iv) previous participation in OS.

A stepwise algorithm based on the Akaike information criterion (AIC) will be implemented to select variables that provide meaningful information independent of the main factors.

SMDM quality will be measured using the DCS and SDM-Q9 scales, responses to participation intent and knowledge of women about the OS. It will be compared between groups using a Student superiority test.

The care pathway of the women responding to the questionnaires will be studied and in particular the concordance between patients’ intention and effective participation in BC screening.

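### The ancillary questionnaire comparison is an unadjusted test among an expected 20% of mailed women, and the article treats low response as a shortage of data but not as a possible source of bias

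*Protocol article*

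**What the plan says.** The second secondary objective (section 2.8.2.2) is the effect of the intervention on shared decision-making. It is measured by postal questionnaire two months after the intervention, in women sampled from both arms. The outcomes are the SDM-Q9 and DCS scores, intention to participate and knowledge.

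- **Size.** Section 2.11.2 takes DCS scores "of 18.53 vs. 13.77 (standard deviation at 20.25" from a published study and concludes that "762 responses would be required to arrive at a significant difference". The questionnaire goes to an "independent sample of 5,000 women, equally divided between the 2 arms". On the expected returns the same section states: "Based on a response rate of 20%, the number of questionnaires collected will be 1,000".
- **Analysis.** Section 2.10.2 gives one between-arm method: "It will be compared between groups using a Student superiority test". Section 2.10 adds: "The materiality threshold will be set at 5% in a bilateral situation".
- **Missing data.** The rules in section 2.10.3 concern the database-derived screening endpoint, where little is expected to be missing. None deals with unreturned questionnaires.
- **Limitation.** Section 3.2 says: "Low response rates to postal questionnaires may limit the available data for this analysis". Its remedies are postage-paid envelopes and a reminder.

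**The concern.** Four in five ancillary outcomes are expected to be missing, and the stated test compares the women who chose to reply. That choice is made after randomisation and after the arms have been treated differently. Section 2.6 has intervention women receive a flyer about the decision aid that encourages them to decide together with their GP, and their GPs receive a letter on the stages of shared decision-making. The questionnaire asks about the same subject. The type of woman who replies, and not only the number, could therefore differ by arm, and randomisation does not protect a comparison conditioned on replying.

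The second secondary objective rests on this comparison. The limitation in section 3.2 would lead a reader to think that enough replies would settle the matter. More replies narrow the interval, but they do not correct a difference in who replies.

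**Working it through.** **Inputs from the article.** DCS means 18.53 and 13.77, SD 20.25, 762 responses required, 5,000 women mailed in equal halves, 20% response (section 2.11.2); two-sided 5% (section 2.10). The power of the ancillary study is not stated.

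**1. Reproduce 762.** The difference is 18.53 − 13.77 = 4.76 points, or 4.76/20.25 = 0.235 SD. With n per arm = 2 × (1.960 + 1.282)² / 0.235², two-sided 5% and 90% power give 381 per arm, 762 in total, an exact match. At 80% power the total would be 570, so 90% was evidently used.

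**2. Is quantity the problem?** 5,000 × 0.20 = 1,000 replies, about 500 per arm. Power for 4.76 points is then 96%, treating women as independent and ignoring clustering by practice. On the plan's own assumptions the number of replies is adequate.

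**3. Precision.** SE = 20.25 × √(2/500) = 1.28 points. Significance needs 1.96 × 1.28 = 2.51 points.

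**4. Error rate under an assumed bias b**, with no true effect: P = 1 − Φ(1.96 − b/SE) + Φ(−1.96 − b/SE).

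| Assumed bias (DCS points) | Two-sided error |
|---|---|
| 0 | 5% |
| 1 | 12% |
| 2 | 35% |
| 2.5 | 50% |

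The bias can also run against a true effect. A true 4.76 points less a bias of 2.5 leaves 2.26, below the 2.51 needed.

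**5. How strong must selection be?** The article gives no figure, so these are assumptions shown as a range. In a normal selection model the mean of responders shifts by ρ × SD × φ(z)/r, where r is the response rate and ρ the correlation between the tendency to reply and the DCS score. At r = 0.20, φ(z)/r = 1.40, so the shift is 28.35 points per unit of ρ.

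- Same ρ and 20% response in both arms: bias 0.
- 20% response in both arms, ρ differing by arm: 2.51/28.35 = 0.09 gives a bias at the significance threshold; 4.76/28.35 = 0.17 gives one the size of the planned effect.
- Same ρ, response 15% v 25%: 5.74 points per unit of ρ. A ρ of 0.1 to 0.5 gives 0.57 to 2.87 points; reaching 4.76 needs ρ = 0.83.
- Same ρ, response 18% v 22%: 2.27 points per unit of ρ. A ρ of 0.1 to 0.5 gives 0.23 to 1.13 points.

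For a yes/no trait with an assumed DCS gap of 10, 15 or 20 points, the imbalance between arms among responders must be about 25, 17 or 13 percentage points to reach 2.51, and 48, 32 or 24 to reach 4.76.

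**6. Are there data for a correction?** Section 2.8.2.1 collects health-system data from before the intervention, and section 2.9 pairs registry and insurance records per woman. Section 2.8.2.2 draws the sample from the trial arms. Together these make baseline data on non-responders likely, but the article does not say so. Section 2.11.2 calls the sample independent, Table 2 and the Ethics statement show a separate ancillary consent and invitation, and the planned linked look at care is limited to responders: "The care pathway of the women responding to the questionnaires will be studied".

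**The case against.** **Left to the full documents.** An article condenses the protocol. Tables of responders and non-responders, weights and sensitivity analyses often sit in the SAP, which is not shown, and naming a Student test does not exclude supporting analyses. This stands: their absence here is not an error in itself. What remains is what the article does fix, namely an unadjusted comparison among responders and a limitation framed as quantity when its own figures show that quantity is covered.

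**Selection as the whole effect.** A reader might infer that selection alone could produce the planned 4.76 points. At 20% response, a 4.76-point difference among responders is compatible with no difference over all 5,000 women if non-responders differ by only 0.2 × 4.76 / 0.8 = 1.19 points the other way. But that identity compares the responder effect with the effect in everyone mailed. It also counts as bias a flyer that really works better in women who open their mail, which limits generalisation but leaves the responder effect real. Bias proper needs selection that differs by arm, and step 5 shows that 4.76 points needs a good deal of it.

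**Data already in hand.** A reader might also infer that baseline data exist for all 5,000 women and are simply unused. Step 6 shows this to be a reasonable inference but not a stated fact.

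**Standing of the analysis.** The comparison is ancillary, listed among exploratory analyses, and presented in section 3.2 as giving initial answers. This stands and limits the weight of the point.

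**Conclusion.** The concern holds in a limited form. The ancillary comparison is open to bias if selection into response differs by arm. The timing and content of the intervention make that plausible, and the article's limitation does not mention it. An arm-dependent bias of 1 to 2.5 DCS points would raise a nominal 5% error to between about 12% and 50%. These biases are assumed: nothing in the article fixes their size, and zero is the right value if selection and response rates match across arms. The calculation also rests on 500 replies per arm, SD 20.25 and no clustering by practice. It is a minor to moderate point on an exploratory outcome. The primary endpoint comes from databases and does not depend on returned questionnaires.

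**What to change.** 1. Report response rates by arm, and the baseline characteristics of responders and non-responders by arm.
2. Confirm that the 5,000 women lie within the trial arms and that non-responders can be linked to registry and insurance records under the ancillary consent arrangements; clarify the word independent in section 2.11.2.
3. If so, set beside the Student test an estimate weighted for the probability of response, fitted by arm on the pre-intervention variables of sections 2.8.2.1 and 2.9, or one adjusted for those covariates.
4. State in section 3.2 that low response may bias the comparison as well as shrink it.

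**Cost.** Some further analysis, and no new data collection if linkage is confirmed. Intervals will be somewhat wider. Since 1,000/762 = 1.31, weighting could inflate the variance by about 31% before power falls below the 90% implied by 762, again ignoring clustering; the actual inflation is unknown until the weights are fitted. Only selection explained by measured variables is removed, so any effect of the flyer on who replies that those variables do not capture would remain.

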## Ethics statement

On 6 December 2021, the protocol received a favorable opinion from the French Committee for the Protection of Persons (2021-A01583-38). The CRCDC will distribute information on the study protocol to healthcare professionals (GPs, gynecologists, midwives) in the region by post 3 months before the intervention. A separate letter informing physicians randomized to the intervention arm of their right not to participate in the research will be sent out during the same period. A letter will be sent informing patients in each arm about their participation in the main study and their opportunity to object. A letter will also be sent inviting patients to answer the ancillary study questionnaires for the and advising them about their freedom of choice to participate. The CRCDC will collect all objections to participation *via* the Data Protection Officer (DPO). Women and GPs will be able to apply to the DPO to be informed of the overall research results.

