### Participants

2.4

Women aged between 50 and 74 years at the start of the study, who are eligible for BC screening, live in the Pays de la Loire region, and are registered with a participating GP will be eligible for inclusion in the study. Any women who are being followed-up for BC or an anomaly, have a medical or family history of BC, have refused or whose GP has refused to participate in the study, have participated in other studies on BC screening, or are under guardianship or curatorship will not be eligible for inclusion. Participating GPs will be the registered GPs for the included women practicing in the Pays de la Loire region. The inclusion and exclusion criteria for women and GPs are shown in **Table 1**. The list of eligible women will be extracted from the CRCDC. The association regular GP-eligible women will be realized by the health insurance system.

**Table 1 T1:** Inclusion and exclusion criteria for GPs and women.

	General practitioner	Women
Inclusion criteria	Specializing in General Medicine (excluding Special Practice Mode)	50 to 74 years old
	Working in Pays de la Loire	Residing in Pays de la Loire
	Having seen more than 100 different patients in the year prior to enrolment	Eligible for organized screening for the month in question
		Present on the patient list of a participating GP
		Affiliated to the health insurance system
Non-inclusion criteria	Refusing to participate in the study	Having a regular GP refusing to participate in the study
	Working in a Health Center	Affiliated with a health center
	Participating in other breast cancer screening studies	Participating in other breast cancer screening studies
		Under curatorship-tutorship
		Excluded from organized screening because they have a history of breast cancer
		Having ongoing follow-up (breast cancer or abnormality or medical surveillance or high-risk woman)

GP, General Practitioner.

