### Randomization

2.5

GPs will be clustered within practices to avoid contamination bias stemming from shared tracking mechanisms and communication among GPs within a practice. As a result, two GPs working in a given practice will be assigned to the same study arm. The women will then be allocated to the same arm as their GP.

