### Participant blinding and informed consent

2.7

The GPs and women in the intervention and control arms will receive a regulatory letter by post informing them that they are participating in a study on screening (**Figure 1**). Opposition to participation in the study is possible in both arms for women and GPs.

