#### Analysis population

2.10.3

Statistical analyses will be performed on all randomized physicians and patients included in the study. As data are collected on medico-administrative databases, very little missing data is expected (only the very rare case of women changing reimbursement schemes). If these women did not have a mammogram as part of the OS at the time of their change of plan affiliation, they will be considered non-participants for the assessment of the primary endpoint in the ITT analysis. Women who died during the study period and had not had a mammogram at the time of death, will also be considered non-participants for the assessment of the primary endpoint. The same applies to women who underwent individual screening during the study period.

A sensitivity analysis on a Per-Protocol population will be performed by removing from the analysis patients for whom a return mail has been received (for example “No longer living at the address indicated”)), patients who have moved outside the Pays de la Loire region, patients who have changed regular GP, patients whose regular GP has ceased to practice during the study period or has died, patients who have been individually screened, who do not enter OS for known medical reasons after the start of the study, or who died during the follow-up period.

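### The protocol conflicts on which GPs are told they may refuse, and excluding refusers' patients after allocation could make the ITT set differ from the randomized one

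*Protocol article*

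**What the plan says.** Four parts of the protocol article bear on GP refusal.

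- **Ethics statement.** General study information goes to healthcare professionals "in the region by post 3 months before the intervention". Then: "A separate letter informing physicians randomized to the intervention arm of their right not to participate in the research will be sent out", in the same period. No matching letter to control GPs is described there.
- **Section 2.7.** On the notice itself: "The GPs and women in the intervention and control arms will receive a regulatory letter by post informing them that they are participating"; the subject named is screening. On refusal: "Opposition to participation in the study is possible in both arms for women and GPs".
- **Section 2.4 and Table 1.** Women are ineligible if they "have refused or whose GP has refused to participate in the study". Table 1 repeats this as a non-inclusion criterion for women, "Having a regular GP refusing to participate in the study", and also lists refusal as a non-inclusion criterion for the GP.
- **Section 2.10.3.** "Statistical analyses will be performed on all randomized physicians and patients included in the study". The per-protocol set is then formed by removing further patients.

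Practices are the unit of randomization (section 2.5), and "The women will then be allocated to the same arm as their GP".

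**The concern.** An intention-to-treat comparison is protected because nothing that happens after allocation decides who is counted. Here one GP's decision removes that GP's whole list of eligible women. If the Ethics statement is followed, that decision is invited after allocation, by a letter described for one arm only.

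If the women of refusing GPs attend screening at a different rate from the others, unequal refusal moves the estimated difference in participation. The margin is 2 percentage points, so a shift of a few tenths of a point matters. Section 2.10.1 requires non-inferiority in both the ITT and the per-protocol sets, but this offers no safeguard: the refusers' women are missing from both.

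**Working it through.** **1. Order of events.** The Ethics statement letter is addressed to GPs who already have an arm, so allocation comes first. Section 2.7 gives both arms a letter and a right to object, but does not say that the letter tells GPs of that right or when it is sent relative to allocation. Table 2 puts the eligibility screen before allocation and main-study consent in the same column as allocation, so it does not settle the order.

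**2. Who is lost.** Under Table 1 the women of a refusing GP are not included, and section 2.10.3 analyses included patients. Refusal is by individual GP. With 2,847 GPs in 1,570 practices (section 2.11.1), or 2,847 / 1,570 ≈ 1.8 per practice, a practice disappears only if all its GPs refuse.

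**3. The plan's own sample size.** Inputs from section 2.11.1: participation 49% in both arms, margin 2 points, two-sided alpha 5%, power 80%, 48 women per cluster, intraclass coefficient 0.05.

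- Per arm: (1.960 + 0.842)² × 2 × 0.49 × 0.51 / 0.02² = 9,808 after rounding up, as stated.
- Design effect: 1 + 47 × 0.05 = 3.35, as stated.
- Total: 19,616 × 3.35 = 65,714 against 65,647 stated, 0.1% apart. The sample size is not in dispute.

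**4. Precision.** With 32,824 women per arm, SE = √(0.49 × 0.51 × 3.35 × 2 / 32,824) = 0.714 points, and power is 80.0%.

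**5. Bias.** Let f1 and f0 be the shares of women lost through GP refusal in the intervention and control arms. Let d1 and d0 be the participation gaps (women of accepting GPs minus women of refusing GPs). The retained mean in each arm shifts by f × d, so

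bias = f1·d1 − f0·d0.

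The protocol states neither f nor d, so every value below is an assumption. The SE allows for the lost women: SE = √(0.49 × 0.51 × 3.35 × [1/(32,824(1 − f1)) + 1/(32,824(1 − f0))]). The chance of a false non-inferiority claim at a true difference of −2 is Φ(bias/SE − 1.96). Power at true equality, if the bias has the opposite sign, is Φ((2 − bias)/SE − 1.96), with bias as its absolute size.

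| f1 | f0 | Gap (points) | Bias (points) | SE | Error at true −2 | Power, opposite sign |
|---|---|---|---|---|---|---|
| 0 | 0 | any | 0 | 0.714 | 2.5% | 80.0% |
| 2% | 0 | 5 | 0.10 | 0.718 | 3.4% | 75.4% |
| 5% | 0 | 5 | 0.25 | 0.723 | 5.3% | 67.7% |
| 10% | 5% | 5 | 0.25 | 0.743 | 5.2% | 65.4% |
| 10% | 10% | 5 | 0 | 0.753 | 2.5% | 75.7% |
| 10% | 0 | 5 | 0.50 | 0.734 | 10.1% | 53.4% |
| 10% | 0 | 10 | 1.00 | 0.734 | 27.5% | 27.5% |

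Equal refusal with equal gaps gives no bias and costs only some power. Unequal refusal with no gap also gives no bias: at f1 = 10% and f0 = 0, power is 77.8%. Harm needs both a difference between arms and a gap. Recruiting more women does not shrink the bias.

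**The case against.** A reader might infer from the Ethics statement that the ITT comparison loses practices from the intervention arm only. The document does not support this. Section 2.7 lets GPs in both arms object, the Ethics statement has all objections collected centrally, and refusal is by individual GP rather than by practice.

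A reader might also infer that GPs refuse knowing their arm. No passage says that the refusal letter discloses allocation. The letter presenting the decision aid is part of the intervention (section 2.6) and is sent at T0, about three months later. Disclosure is plausible but not stated.

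The size is equally open. The plan expects approximately all 2,847 GPs to be included, so refusal may be rare, and at 2% with a 5-point gap the error barely moves. Nothing in the document shows that the patients of refusing GPs attend screening less, or more. This is also a condensed article, and the study-design figure cited in section 2.7 is not available here, so the intended sequence may be clearer elsewhere.

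These points remove any claim of one-sided loss, of a known direction or of a known size. They leave three things standing: the two passages disagree, the one passage that specifies a refusal letter places it after allocation in one arm, and the exclusion rule acts on whatever refusals follow.

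**Conclusion.** The concern holds as a conflict between section 2.7 and the Ethics statement, with a resulting risk of differential exclusion after allocation. The set called ITT may not be the randomized one, and refusals would probably be more frequent in the intervention arm if the Ethics statement is followed.

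The effect could be negligible, or it could use up a material part of the 2-point margin. With no control-arm refusal and a 5-point gap, it runs from 0.1 point at 2% refusal to 0.5 point at 10%. These figures rest wholly on assumed refusal shares and gaps, and the sign is unknown: the bias could equally produce a false claim of non-inferiority or the loss of a true one.

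This should be fixed rather than treated as a proven fatal flaw. It is best done before allocation and mailing, since the analysis cannot fully undo the selection afterwards.

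**What to change.** - Reconcile sections 2.4 (with Table 1), 2.7 and 2.10.3 and the Ethics statement on which GPs are notified, when, and what follows from refusal.
- Send one identical, neutral opposition notice, which does not name the decision aid, to all eligible GPs in the mailing already planned three months before the intervention. Close the opposition window, then randomize the remaining practices. Refusals then cannot depend on the arm.
- For a GP who refuses after allocation, keep the women in their allocated arm for the ITT analysis where the objection and data rules allow it. This changes a Table 1 criterion, and section 2.15 speaks of data on women and professionals willing to take part, so it needs checking first. Where it is not allowed, report GP refusals and women lost by arm, with a sensitivity analysis over plausible gaps.

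**Cost.** Mailing and allocation are re-ordered, a letter goes to the control GPs (about 2,847 / 2 ≈ 1,424), and an ethics submission is needed. Late refusers kept in the ITT set dilute the intervention slightly. Refusals before randomization reduce numbers in both arms, but the three-month recruitment potential of 3 × 25,000 = 75,000 women exceeds the 65,647 required. A loss of up to 1 − 65,647 / 75,000 = 12.5% from all causes, including women's own objections, could be absorbed.
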